### Study design

2.1

The PrimerX study is conducted within the Dutch Prospective Renal Cell Carcinoma (PRO-RCC) cohort [25]. The PRO-RCC cohort includes patients with metastatic and nonmetastatic renal cancer, and has been designed for prospective collection of long-term clinical data, patient-reported outcome measures, and patient-reported experience measures. Furthermore, the PRO-RCC cohort can be used as an infrastructure for initiating TwiCs studies [26]. The PrimerX study follows this TwiCs study design (Fig. 1). In addition, a Bayesian adaptive multistage design is applied to allow for early stopping for futility or efficacy. Synchronous mRCC patients will be randomised to local therapy (deferred CN or any form of local ablative therapy; experimental intervention) or to a control arm that receives the SOC, in principle without CN. The primary objective is to reassess the benefit of deferred CN in the current immunotherapy era, by a preset analysis of the OS clinical endpoint.

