Primary tumour in situ
Participation in the PRO-RCC prospective cohort

IO = immune oncology; PRO-RCC = Dutch Prospective Renal Cell Carcinoma; RCC = renal cell carcinoma; TKI = tyrosine kinase inhibitor.

Patients who are randomised to the experimental arm will be counselled by their treating physician for participation in the experimental arm. If these patients accept the intervention, they are asked to sign an additional informed consent form containing all information regarding the PrimerX study, as part of the staged informed consent procedure [29]. Patients who refuse the offered experimental intervention will continue to receive the SOC. Patients randomised to the control arm will receive no additional consent for the TwiCs study, and thus not informed about the experimental intervention or about their participation in the study as controls (Fig. 1), based on their consent upon entry in the cohort. Patients randomised to the control arm will receive the SOC.

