### Experimental intervention

2.5

The experimental intervention consists of (partial) CN or any ablative local therapy between 6 mo and 1.5 yr after the start of systemic treatment. All types of ablative local therapies are allowed as a substitute for CN, including magnetic resonance imaging–guided stereotactic radiation. The patients’ physician chooses the treatment plan and the modality used for tumour ablation. Randomisation occurs after at least 6 mo of ICI combination therapy, as stated in Figure 2. Patients who discontinue their first-line treatment due to progression at metastatic sites in the timeframe between randomisation and local therapy are disqualified for local treatment but continued in the TwiCs study in order to be part of the intention-to-treat (ITT) analysis. The same applies for patients who are randomised to the experimental arm but who refuse local treatment. All these patients will be treated according to the SOC. Patients in the experimental arm will be asked for additional sampling of blood after the local intervention.

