### Analysis plan

2.8

Analyses are conducted on an ITT basis. An ITT analysis in a TwiCs study represents the average causal effect of offered treatment, and the intercurrent event noncompliance in the experimental intervention arm is handled according to the treatment policy strategy [31]. At the interim analyses, provisional efficacy will be concluded when the posterior probability of HR <0.9 exceeds the efficacy stopping boundaries, as listed in Table 2. If this happens at an interim analysis, recruitment is stopped, but follow-up is continued. The trial will stop for futility as soon as an interim analysis reveals that the posterior probability for an HR of <0.9 drops below the futility stopping boundaries, as listed in Table 2.

If the maximum sample size has been reached or accrual has been halted based on the efficacy stopping rules, a final analysis will be conducted using the log-rank test for OS after the completion of 5-yr follow-up for all patients. Efficacy of the experimental intervention at the final analysis will be concluded when the one-sided *p* value of this final log-rank falls below 0.05. The OS curve will be constructed using the Kaplan-Meier method. In addition, a per-protocol analysis will be performed. Moreover, ITT and per-protocol subgroup analyses will be performed for subgroups based on the type of local treatment and type of systemic treatment.

In addition, Fisher exact test will be used to compare the treatment arms on objective response rate and surgical morbidity. Follow-up QoL will be assessed by linear mixed models adjusting for baseline score, including treatment group and time as fixed covariates and treating patients at random.

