We took great care to establish median OS estimates for the sample size calculation. The majority of patients presenting with mRCC and the primary tumour in place belong to the IMDC intermediate- and poor-risk categories. In a recent 5-yr update of IMDC intermediate- and poor-risk patients treated with nivolumab and ipilimumab, the median OS was 47 mo. However, for patients with synchronous mRCC, this is likely an overestimation, as 78% of the patients in the CheckMate-214 trial had metachronous disease. The HR for OS in that trial was 0.68 in favour of the combination, resulting in a 32% reduction in the hazard of death compared with sunitinib. Based on the median OS results in the sunitinib-alone arm in the CARMENA trial, the median OS can be deduced for a population of patients with synchronous mRCC treated with nivolumab and ipilimumab. Two other trials investigating deferred CN in combination with ICI therapy in the USA and Scandinavia, using a classical RCT design, used similar median OS estimates of 24 mo [35], [36]. However, they underestimated the survival gain achieved by excluding patients with no clinical benefit following ICI therapy from randomisation, which reduces the event rate and requires larger sample sizes.

PrimerX is not designed to investigate the role of deferred CN in combination with a specific first-line standard, nor is it suited to study the optimal time point for an intervention. However, the lessons learned from the EORTC SURTIME trial demonstrate that complexity in surgical trials jeopardises accrual. Evidence from CARMENA and SURTIME suggests that deferred CN can be considered upon documentation of a sustained response to systemic therapy rather than at a specific point in time. In addition, we believe that removal of the primary tumour should be investigated as a concept in the multimodality management of mRCC rather than as a specific approach. While nephrectomy has evolved as the gold standard for cytoreduction, recent data suggest that thermal ablation or stereotactic ablative body radiotherapy may be equally effective in smaller tumours. As ICI combination therapy may downsize primary tumour diameters by >70%, PrimerX specifically allows alternative local therapies in the experimental arm.

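### Type of local treatment cannot define an ITT subgroup: it is the physician's choice, apparently made after allocation, and is undefined for about 54% of the patients

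*Protocol article*

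**What the plan says.** The Analysis plan (2.8) defines the ITT estimand: "An ITT analysis in a TwiCs study represents the average causal effect of offered treatment". It then adds a per-protocol analysis and states that "ITT and per-protocol subgroup analyses will be performed for subgroups based on the type of local treatment and type of systemic treatment".

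Other sections describe how a patient comes to have a type of local treatment:

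- Experimental intervention (2.5) allows several modalities: "The experimental intervention consists of (partial) CN or any ablative local therapy between 6 mo and 1.5 yr after the start of systemic treatment". The patient's "physician chooses the treatment plan and the modality used for tumour ablation".
- Eligibility criteria (2.4) places the discussion of the intervention after allocation, in one arm: "Patients who are randomised to the experimental arm will be counselled by their treating physician for participation in the experimental arm".
- Study design (2.1) describes a "control arm that receives the SOC, in principle without CN". Under 2.4, controls are "thus not informed about the experimental intervention or about their participation in the study as controls".
- SOC treatment (2.6) lets the physician offer a control patient deferred nephrectomy when the primary tumour progresses, or when metastatic sites have responded completely.
- Under 2.5, experimental patients who refuse, or whose metastases progress before local therapy, receive no local treatment but stay in the ITT set.

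**The concern.** An ITT subgroup comparison is randomised only if the subgroup can be identified in both arms by something that allocation cannot influence. Type of local treatment fails on both counts. It comes into being with treatment, almost entirely in one arm, and depends on the patient's acceptance, course and physician.

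At stake is the meaning of any modality-specific hazard ratio. Labelled as ITT, it would carry the authority of randomisation and could be read as showing that nephrectomy works and ablation does not, or the reverse. It could instead reflect which patients were given which procedure. The Discussion gives a concrete reason to expect such selection, since it links ablative options to tumour size: "recent data suggest that thermal ablation or stereotactic ablative body radiotherapy may be equally effective in smaller tumours".

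**Working it through.** The plan gives no figure for this analysis, so there is none to reproduce. The point is one of logic; the arithmetic shows its size.

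**1. Who has a type of local treatment?**

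Inputs from 2.7: 350 patients per arm, 15% refusal in the experimental arm, about 7% deferred nephrectomy in the control arm.

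- Experimental patients with no type, refusal alone: 0.15 × 350 = 52.5.
- Controls with no type: 0.93 × 350 = 325.5.
- Together: 52.5 + 325.5 = 378 of 700, or 54%.

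Patients who progress before local therapy would add to this, but the article gives no rate for them. Section 2.7 also describes refusal as one in six and gives 60 of 754 (8.0%) for deferred nephrectomy. With those values the total is 350/6 + 350 × (1 − 60/754) = 58.3 + 322.1 = 380.5, still 54%.

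**2. Can the controls who have a type serve as comparators?**

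They number about 0.07 × 350 = 24.5. Under 2.6 they reach nephrectomy through progression of the primary tumour or complete response at metastatic sites, both seen during follow-up. Experimental patients reach it through allocation and acceptance. The two groups are selected differently, so comparing them is not a randomised comparison.

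**3. What if recipients of each modality are compared with all controls?**

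*Immortal time.* A patient counted as treated must have survived from randomisation to local therapy. Take a constant hazard λ, no treatment effect, a delay of d weeks and follow-up of F weeks. With P = 1 − exp(−λ(F − d)), recipients have P deaths per patient over d + P/λ weeks, while controls die at rate λ. The apparent rate ratio, used here as the hazard ratio, is

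HR = P / (λd + P).

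Inputs: λ = 0.0043 per week (2.7); F = 260 weeks (the 5-year minimum in 2.8) and 364 weeks (7 years, assumed for early entrants). The delay d is not given in the article and is varied.

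| d (weeks) | λd | P at F = 260 | HR | P at F = 364 | HR |
|---|---|---|---|---|---|
| 4 | 0.0172 | 0.667 | 0.97 | 0.787 | 0.98 |
| 13 | 0.0559 | 0.654 | 0.92 | 0.779 | 0.93 |
| 26 | 0.1118 | 0.634 | 0.85 | 0.766 | 0.87 |

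This counts deaths only. Recipients must also be free of metastatic progression until therapy, which would add bias in the same direction.

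*Selection by prognosis.* As an illustration, assume no treatment effect, that physicians steer the better-prognosis half to one modality, and that the hazards of the two halves differ by a factor r. The halves then have hazards λ/√r and λ√r, and all controls have the pooled rate. Over 260 weeks:

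- r = 1.25: apparent HR 0.89 for one modality, 1.12 for the other.
- r = 1.5: 0.82 and 1.22.
- r = 2: 0.70 and 1.41.

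The values of r and the even split are assumptions. The trial's interim analyses judge success on the probability of an HR below 0.9 (Table 2), so spurious differences of this order would be large enough to mislead.

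**4. Does the same objection apply to type of systemic treatment?**

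No. Under 2.4 and 2.5 patients have had at least 6 months of that therapy before randomisation. The factor exists in both arms and allocation cannot alter it.

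**The case against.** Several points can fairly be made for the plan.

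- **The comparison is not spelled out.** The article does not say that each modality will be set against all controls, and a full protocol or SAP may define the groups. Grouping by modality offered rather than received would remove the need to survive to treatment. This stands as far as the bias figures go: they describe one natural implementation. It does not rescue the statement itself, because the article positively promises an ITT subgroup by type of local treatment, and no randomised version can be formed from what it describes.
- **The timing is inferred.** Section 2.5 says who chooses the modality, not when. Surgeon and anaesthetist assessment is an eligibility criterion, so some planning may precede allocation. This stands, and the wording here is accordingly that the choice apparently follows allocation. The article mentions no intended modality recorded for all patients beforehand.
- **Fitness is partly controlled.** Everyone must be a surgical candidate with performance status 0 or 1. This narrows confounding by fitness but leaves tumour size and response.
- **The article limits its own claim.** The Discussion says that removal of the primary tumour is to be studied as a concept rather than as one specific approach. That weakens the prospect of a modality claim and is also a reason not to plan the contrast.

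A reader might go further and infer that the analysis is impossible because no control has a type of local treatment. The documents do not support that: about 7% of controls are expected to have one, and a non-randomised contrast can be computed. Nor do they support one fixed bias figure, since the delay from randomisation to local therapy is not stated.

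**Conclusion.** The concern holds for the analysis as labelled. Type of local treatment is undefined for about 378 of 700 patients (54%) on the plan's own rates. Where it is defined, it follows from selection after randomisation, so it supports no ITT comparison within a modality. That conclusion rests on the logic of the design and on the 15% and 7% rates. It also takes the order of events in 2.4 and 2.5 to mean that the modality is settled after allocation.

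The bias from an as-treated contrast against all controls is illustrative. Under no effect, immortal time alone gives an apparent HR from about 0.98 down to 0.85 for delays of 4 to 26 weeks. This assumes a constant hazard of 0.0043 per week and 5 to 7 years of follow-up. Selection by prognosis could move the result in either direction.

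A reader might infer that the trial's main conclusion is at risk. It is not: efficacy rests on the final ITT log-rank test, which this subgroup does not touch. The point is a correction to a non-primary analysis that should be made.

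**What to change.** In 2.8, remove type of local treatment from both the ITT and the per-protocol subgroup comparisons. Report outcomes by modality descriptively, within the experimental arm and without a contrast to control. Keep type of systemic treatment, as fixed at randomisation, as the subgroup factor.

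This costs a change of wording and no new data. The only loss is that no modality-specific treatment effect is claimed.

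Recording an intended modality for every eligible patient before allocation would in principle give a valid factor, but it is the weaker choice. Surgical candidacy is required of everyone, so it cannot separate nephrectomy from ablation, and a new judgement would be needed. Asking physicians to name a procedure for future controls could also prompt more deferred nephrectomy in that arm and so raise control dilution.

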## Discussion

3

The SURTIME and CARMENA trials were performed prior to the availability of ICIs, when VEGFR TKIs were the mainstay of systemic treatment. Given the benefit of CN in the setting of first-generation immunotherapy, it is conceivable that both trials underestimated the benefit of CN in the absence of immunotherapy. Hence, the benefit of deferred CN or local therapy needs to be reassessed in the context of ICI combination therapy.

The current guidelines from the European Association of Urology suggest that in patients showing a clinical response to ICI-based combinations, subsequent CN may be considered [20]. However, it is important to note that this recommendation is based on weak evidence. Therefore, the purpose of this study is to either confirm or refute the existing limited evidence.

Performing CN after prior ICI combination therapy appears to be safe with pathologically favourable tumour characteristics, although the numbers reported are limited. Considering the limited risks involved, the significance of addressing this research question outweighs the potential drawbacks.

This study is designed as a TwiCs study, which has some appealing characteristics compared with the classical RCT. Classical RCTs are often confronted with slow recruitment, a disappointment bias in patients randomised to the control arm leading to potential dropout, and limited external validity. The TwiCs trial design was introduced to overcome these shortcomings [26]. Since patients in the control arm are not informed about the experimental deferred CN, they are unlikely to be discouraged by not being offered a new treatment, thus preventing dropout. In addition, the observational cohort represents the population more adequately because cohort studies are generally less selective when including patients. This can prevent the selection bias when recruiting patients for a TwiCs study (see, eg, the study of Gal et al [32]).

Furthermore, this TwiCs trial incorporates a Bayesian adaptive multistage trial design with a flexible number of patients to be included, ensuring that only patients who are actually needed to reach conclusions will enter the trial. In addition, the Bayesian approach for interim analyses is more flexible than the frequentist approach since early stopping does not affect Bayesian inference, and hence, multiplicity issues do not play a role [33]. To our knowledge, this is the first TwiCs study design that follows a Bayesian adaptive multistage trial design, thereby possessing multiple advantages and flexibilities compared with the classical way of conducting RCTs.

A challenge of a TwiCs study is the anticipated refusal rate in the experimental arm and how this affects the ITT effect and initial sample size calculations. Some previous TwiCs studies in oncology have been proved to underestimate the refusal rate, and sample sizes had to be increased during the trial [31]. This is also a potential risk for the current trial, which is why we have incorporated two early interim checks to monitor the refusal rates and prematurely stop the trial in case the refusal rate is much larger than expected. In addition, we have simulated a trial scenario in a situation where initial refusal rates are underestimated, in which we follow the recommendation to evaluate trial scenarios under different refusal rate assumptions [34].

We took great care to establish median OS estimates for the sample size calculation. The majority of patients presenting with mRCC and the primary tumour in place belong to the IMDC intermediate- and poor-risk categories. In a recent 5-yr update of IMDC intermediate- and poor-risk patients treated with nivolumab and ipilimumab, the median OS was 47 mo. However, for patients with synchronous mRCC, this is likely an overestimation, as 78% of the patients in the CheckMate-214 trial had metachronous disease. The HR for OS in that trial was 0.68 in favour of the combination, resulting in a 32% reduction in the hazard of death compared with sunitinib. Based on the median OS results in the sunitinib-alone arm in the CARMENA trial, the median OS can be deduced for a population of patients with synchronous mRCC treated with nivolumab and ipilimumab. Two other trials investigating deferred CN in combination with ICI therapy in the USA and Scandinavia, using a classical RCT design, used similar median OS estimates of 24 mo [35], [36]. However, they underestimated the survival gain achieved by excluding patients with no clinical benefit following ICI therapy from randomisation, which reduces the event rate and requires larger sample sizes.

PrimerX is not designed to investigate the role of deferred CN in combination with a specific first-line standard, nor is it suited to study the optimal time point for an intervention. However, the lessons learned from the EORTC SURTIME trial demonstrate that complexity in surgical trials jeopardises accrual. Evidence from CARMENA and SURTIME suggests that deferred CN can be considered upon documentation of a sustained response to systemic therapy rather than at a specific point in time. In addition, we believe that removal of the primary tumour should be investigated as a concept in the multimodality management of mRCC rather than as a specific approach. While nephrectomy has evolved as the gold standard for cytoreduction, recent data suggest that thermal ablation or stereotactic ablative body radiotherapy may be equally effective in smaller tumours. As ICI combination therapy may downsize primary tumour diameters by >70%, PrimerX specifically allows alternative local therapies in the experimental arm.

